#### Study 2: Structure and process evaluation of GEDI

This qualitative phase of the research aims to examine the structures and processes required for effective implementation of a GEDI MOC and staff and patient experience of the model [38, 44]. The structures and processes required for the GEDI MOC evaluation were adapted from Irvine et al.’s (1998) nursing role effectiveness model [45]. Structural elements required to operate GEDI include organisational, patient and staff resources. Process elements include role and relationship requirements that enable the GEDI MOC to operate, such as team communication, nursing interventions and case management.

The focus is on frail older persons living in the community or RACF with acute and chronic medical conditions, their family and the staff interacting with GEDI MOC.

##### Participants

There are two participant groups:Nursing and Medical staff - NGH ED (*n* = 20). Participants in this group will have worked with the GEDI team in the ED.Frail older persons living in the community or RACF who presented to the ED and were seen by the GEDI team and/or their family member (*n* = 10). Participants in this group will have had personal experience or family member experience of their relative being cared for by the GEDI team.

Participants will be recruited via the following methods:Emails will be sent to all ED staff via the CNC/Nurse Unit Manager and Medical Director of the ED. A member of the research team will attend staff meetings. Interested staff will then be provided with an information sheet and consent form and an interview arranged at a time and place suitable to the participant.Older persons, RACF residents and/or their attending family members will be given an information sheet, consent form and reply paid envelope while in the ED. This group will be sampled via purposeful sampling to obtain information rich cases who have experienced the GEDI MOC. Consent will be obtained in writing at the time of the interview.

##### Data collection

Semi-structured, audio-recorded, individual interviews will be undertaken. Participants will be asked to respond to semi-structured questions framed around the a priori system of catagorising qualitative data as proposed by Bogdan and Biklen [46]. These a priori categories will be delineated by the structures and processes required for the GEDI MOC evaluation, adapted from Irvine et al.’s (1998) nursing role effectiveness model [45]. Recorded interviews will be transcribed verbatim prior to analysis.

##### Data analysis

A priori categorisation ensures the analysts code the interviews relevant to the research questions during the analysis [47]. For each section of qualitative data relating to the relevant a priori category, the transcripts of interviews are read and re-read with an initial label then assigned to sections of text. The use of a priori labels provides a separate accounting scheme for the analysis of qualitative data by limiting the analysis to focus on the structures and processes experienced by participants relevant to the GEDI MOC. Development of categories by assigning textual data to emerging categories, enable comparison and discussion with the research team [48]. NVivo 10 will be used to manage the transcribed interview data.

#### Study 3: Health economics

Individual patient data will be collected from the Hospital Based Corporate Information System (HBCIS) for Nambour General Hospital. HBCIS is a patient record system for hospital administration that includes information such as patient details, ED presentation complaint, diagnosis, length of stay, bed and menu assignment, discharge status and costs associated with ED episode and inpatient episode of care (if the patient was admitted for inpatient care). For the economic analysis, data will be collected from the two periods in time pre and post GEDI MOC implementation. The historical data during the period of 1^st^ January 2012 – 31^st^ December 2012. The experimental data will be collected for the period of 1^st^ September 2015 to 31^st^ August 2016. While de-identified, the costing data contains sufficient information on hospital resource utilisation such as triage category, length of stay, and treatment received as well as discharge status.

##### Data analysis

A multivariate cost function will be estimated to determine average cost per patient, for before- and after-GEDI MOC scenarios. The function takes into account important determinants of individual cost such as age, severity, length of stay and procedures received while in the ED. In the cost effectiveness analysis, we will estimate the average difference in number of admissions for the before- and after-GEDI scenarios. The number of avoidable admissions will be converted to cost savings using the results of the cost analysis above, and compared against the implementation cost for the GEDI MOC. If the cost savings is larger than the implementation cost, the GEDI MOC can be viewed as cost effective.

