### Intervention

GEDI is a nurse-led, physician-championed innovative MOC that aims to reduce frail older person living in the community or RACF ED length of stay and streamline service delivery by maximising the provision of care during the patient’s ED journey. GEDI clinical nurses (CN) have a minimum of five years post registration experience and specialist expertise and/or education in both emergency nursing and care of the older person. Their role focuses on case-managing frail older persons living in the community or RACF in the ED facilitating rapid access and coordination of care through ED, hospital and community services.

There are 2.4 full time equivalent (FTE) GEDI CNs and a 0.8 FTE Clinical Nurse Consultant (CNC) employed by the ED. They cover the ED from 0700 to 1730 Monday to Friday and 0700 to 1530 on weekends. The GEDI CNC oversees the CN role, providing education, leadership, managerial oversight of the service and clinical support where needed. An ED physician provides medical leadership and together with the CNC they are responsible for research and administration.

In the ED, the GEDI team will provide early, rapid, targeted geriatric assessment of frail older persons living in the community or RACF presenting to the ED and, through careful inter-facility and interdisciplinary, management and planning, aim to prevent unnecessary admissions to hospital. In addition, the GEDI CNs provide a single point of contact for ED and RACF staff who may be having difficulty managing an older person with an acute illness. Table 1 outlines the elements included in the GEDI roles. The importance of the ED clinical experience required for the GEDI role relates to the need for GEDI CNs to optimise communication; multitask within a chaotic, fast-paced clinical environment; and be familiar with the staff, clinical pathways and protocols.

**Table 1 Tab1:** GEDI team responsibilities

GEDI Clinical Nurse Consultant	GEDI Clinical Nurse	GEDI Physician
Clinical responsibilities		
▪ Collaborative partnership with physician-champion to develop evidenced based guidelines specific to the needs of the geriatric patients and clinicians in the ED	▪ Works collaboratively with all ED staff	▪ Clinical resource and expert in geriatric emergency medicine

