▪ Develops and maintains enhanced communication strategies related to ED staff, RACF staff, Nurse Practitioner (NP), community services, paramedic staff and general medical practitioners (GPs).	▪ Enhanced communication by providing a dedicated single point of contact within the ED for RACF staff, NP, community services, paramedics and GPs to obtain support and advice regarding optimal care and management of acutely unwell or injured frail older person or RACF resident	▪ Facilitates interdisciplinary discussions and establishes clinical hospital wide networks
▪ Develops and upskills CNs in use of rapid assessment of frail older persons or RACF residents	▪ Rapid assessment and management of frail older persons or RACF resident including nurse initiated analgesia and investigations	▪ Identify information to be sourced by the GEDI CN relevant to ED medical officers
▪ Develops evidence based clinical care algorithms for common problems experienced by RACF residents within the ED	▪ Provides evidence based clinical care for older persons in the ED in collaboration with the primary nurse	▪ Provide education for emergency staff, promoting informed decision making and best practice
▪ Provision of a consultative service for patient centred care of the frail older person or RACF resident within the ED	▪ Provision of a consultative service for patient centred care of the frail older person or RACF resident within the ED	
▪ Develops systems and upskills CNs to undertake direct referral to Geriatricians and rapid consultation pathways with other medical service streams	▪ Direct referral to Geriatricians and rapid consultation pathways with other medical service streams	
▪ Develops systems to facilitate pre-hospital communication with the RACF, GP, NP and Ambulance service, facilitating appropriate transfer decision making and early arrival triage	▪ Pre-hospital communication with the RACF, GP, NP and Ambulance service, facilitating appropriate transfer decision making and early arrival triage	
	▪ Liaison with hospital acute-care substitution services such as the Hospital in The Home and palliative care services	
Administrative responsibilities		
▪ Collaborative partnership with physician-champion to manage the GEDI team and GEDI CN portfolios	▪ Facilitation of discharge back to place of residence or admission – i.e. appropriate disposition planning	▪ Implement MOC and promote care of the older persons in ED

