### Study design

Pragmatism will provide the philosophical paradigm for this mixed model evaluation research. This philosophical paradigm allows the researcher to focus on “what works” and provides solutions for problems utilising methods that best meet their needs and purpose [37]. The design will be underpinned by Donabedian’s structure, process and outcome evaluation of healthcare framework [38].

The three studies included in this protocol will aim to answer the following evaluative research questions:What is the effect of the introduction of the GEDI MOC on the outcomes of frail older persons living in the community or RACF who present to ED? (Outcomes include: rates of ED representation within 72 h and 28 days, mortality, ED and hospital LoS, time to referral and hospital admission rates).What structures and processes are required to deliver the GEDI MOC?Specifically:What are the experiences of staff in regards to the processes of the GEDI MOC?What processes pertaining to the GEDI MOC have affected the day to day operation of the ED, and how?What are the residents’ and carers’ experiences of the GEDI MOC?
What is the effect of the GEDI MOC on hospital and health service delivery costs?Specifically:What is the effect of the introduction of the GEDI MOC on per patient cost associated with ED and hospitalisation?What is the effect of the introduction of the GEDI MOC on preventing the costs associated with avoidable inpatient admissions?

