## Discussion

GEDI is an innovative MOC that provides a single point of contact in the ED for RACF staff, primary health services and secondary health services. The primary focus is to deliver high quality care for frail older persons living in the community or RACF through seamless continuity of care as they transition through the ED. Secondly, the GEDI MOC aims to facilitate community care strategies and thus acts as a hospital substitution model.

Complex, multifocal interventions, such as the GEDI MOC, are frequently implemented without rigorous evaluative research. This study will provide not only a description of the structures and processes required for successful implementation of the MOC but will also provide older person and cost related outcomes.

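### Study 3's rule for calling GEDI cost effective has no term for care that replaces an avoided admission, so it can support only a claim about Nambour ED and inpatient costs

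*Protocol article*

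**What the plan says.** The economic decision rule is in the Protocol article, Study 3: Health economics, Data analysis. A multivariate cost function gives an average cost per patient before and after GEDI. The difference in number of admissions is estimated, and then "The number of avoidable admissions will be converted to cost savings using the results of the cost analysis above". That sum is set against the cost of implementing GEDI. If the saving is larger, the model is viewed as cost effective.

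The cost inputs come earlier in Study 3: "Individual patient data will be collected from the Hospital Based Corporate Information System (HBCIS) for Nambour General Hospital". The costs listed are "costs associated with ED episode and inpatient episode of care (if the patient was admitted for inpatient care".

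Three other places bear on what those inputs should cover:

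- Intervention: the team will "aim to prevent unnecessary admissions to hospital". Table 1 lists among the clinical nurse's duties "Liaison with hospital acute-care substitution services such as the Hospital in The Home and palliative care services".
- Discussion: as its second purpose, "the GEDI MOC aims to facilitate community care strategies and thus acts as a hospital substitution model".
- Study design, research question 3: "What is the effect of the GEDI MOC on hospital and health service delivery costs". Two specific sub-questions follow, one on per-patient ED and hospitalisation cost and one on the cost of avoidable inpatient admissions.

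**The concern.** The protocol describes an intervention that, for some patients, replaces a hospital stay with care elsewhere. The rule values the stay that did not happen and gives no value to the care that took its place. Hospital in the Home, palliative care and community services all cost something, and no such cost is named among the inputs.

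The conclusion is what is at stake. A cost moved from the inpatient budget to another part of the health service would meet the rule just as a real saving would. The study could then report GEDI as cost effective, under a research question about health service delivery costs, when part or all of the saving had only been moved. The article states the benefit side, the cost side and the verdict in full, so this is not a detail left to a longer document.

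**Working it through.** The documents give no unit cost, number of avoided admissions or implementation cost, so there is no stated figure to reproduce. The check is the algebra of the rule, with assumed values to show the scale.

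**Inputs**

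- N: avoided admissions (Study 3, Data analysis; no value given).
- C: cost credited per avoided admission, from the cost function (same place; no value given).
- I: implementation cost (same place; no value given).
- f: share of avoided admissions that receive substitute care (not in the documents; assumed).
- s: cost of that care as a fraction of C (not in the documents; assumed).

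**Step 1. The rule as written.** GEDI is cost effective if N × C > I. With R = N × C / I, this is R > 1.

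**Step 2. The rule with substitute care counted once.** The saving becomes N × C − N × f × s × C = N × C × (1 − f × s). The test becomes R × (1 − f × s) > 1.

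**Step 3. The difference.** The written rule exceeds the netted one by N × f × s × C. Neither f nor s can be negative, so for N > 0 this term is zero or favours GEDI. It is zero if no avoided admission is replaced by paid care.

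**Step 4. Break-even.** The verdict reverses when f × s > 1 − 1/R.

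| R (assumed) | 1 − 1/R | Break-even f × s |
|---|---|---|
| 1.1 | 1 − 0.909 | 9.1% |
| 1.25 | 1 − 0.800 | 20% |
| 1.5 | 1 − 0.667 | 33.3% |
| 2 | 1 − 0.500 | 50% |
| 3 | 1 − 0.333 | 66.7% |

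**Step 5. Example.** Take R = 1.5. At f × s = 0.3 the netted ratio is 1.5 × 0.7 = 1.05, and the verdict just survives. At f × s = 0.5 it is 1.5 × 0.5 = 0.75, and the verdict reverses.

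The product f × s is what matters. If 60% of avoided admissions were replaced by care at half the cost of the admission, f × s would be 0.6 × 0.5 = 0.3. Treating every avoided admission as replaced (f = 1) would be the extreme case.

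**The case against.** The strongest reply concerns perspective. The wide wording of research question 3 is narrowed at once by its two sub-questions, which ask about ED and hospitalisation cost and about avoidable inpatient admissions. The Study 3 data and analysis match those sub-questions, so the protocol can fairly be read as taking a hospital perspective. This stands, and it rules out saying that a whole-system costing was promised and not delivered. It does not rescue the verdict, because the rule's conclusion is not limited to that perspective.

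The mechanism should not be overstated either. Substitution is the second purpose in the Discussion, and Table 1 speaks of liaison. An unnecessary admission may need no replacement at all. This stands and is the reason for including f. Nor does the text say that the full cost of an admission is credited. It says that the results of the cost analysis are used, and it states no offset. The description of HBCIS contents is illustrative, so some substitute care might be recorded there, though nothing says that it is.

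A reader might infer two stronger points that the documents do not support:

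- **That the overall verdict is biased towards GEDI.** Only the omitted term has a known sign. The rule credits only the difference in number of admissions, so savings from shorter ED or hospital stays, or from fewer re-presentations, may also go uncounted and act the other way.
- **That Hospital in the Home patients or transfers will be miscounted as avoided admissions because Study 1's four dispositions have no code for them.** The documents do not say how such patients are coded. Study 3 draws on discharge status in HBCIS, whose categories are not given, and nothing suggests that GEDI increases transfers.

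**Conclusion.** The point holds in a limited form. The stated rule has no term for replacement care, the protocol itself describes such care as part of GEDI's function, and the only costs named are ED and inpatient episodes at one hospital. For the avoided admissions that are replaced by other paid care, the saving is overstated by f × s × C on average across all avoided admissions.

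Whether this would change the verdict cannot be determined from the documents. A narrow margin is fragile: at R = 1.1 a product of about 9% is enough. At R = 2 it would take 50%. These figures rest on assumed values of R, f and s, and on other unmodelled savings being left aside. What can be said without assumptions is that meeting the rule shows a favourable cost offset within Nambour's ED and inpatient costs. It does not show cost-effectiveness or lower health service delivery costs.

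**What to change.** In Study 3, Data analysis:

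1. State the hospital perspective that the sub-questions of research question 3 imply. Word the conclusion as: the Nambour ED and inpatient cost offset exceeds (or does not exceed) the implementation cost. Do not use the terms cost effective or health service delivery costs for this result.
2. Report the break-even f × s = 1 − 1/R, with R as observed, as a sensitivity analysis. Readers can then judge whether substitute care could plausibly reach it.
3. Where Hospital in the Home or other health service episodes can be identified in the linked data for both periods, subtract their cost once from the saving. Do not also remove those patients from the count of avoided admissions, because that would deny the credit and still make the charge, which biases against GEDI.

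The first two steps need only wording and one line of arithmetic. The third depends on what the health service's linked EDIS, HBCIS and financial data contain. The documents do not say that Hospital in the Home is included, so this step is conditional. The cost is a little extra analysis and a narrower or less favourable claim.

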## Abstract

**Background:**

Emergency departments are chaotic environments in which complex, frail older persons living in the community and residential aged care facilities are sometimes subjected to prolonged emergency department lengths of stay, excessive tests and iatrogenic complications. Given the ageing population, the importance of providing appropriate, quality health care in the emergency department for this cohort is paramount. One possible solution, a nurse-led, physician-championed, emergency department gerontological intervention team, which provides frontload assessment, early collateral communication and appropriate discharge planning, has been developed. The aim of this Geriatric Emergency Department Intervention is to maximise the quality of care for this vulnerable cohort in a cost effective manner.

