## Methods/design

### Study aims

The aims of the Geriatric Emergency Department Intervention (GEDI) MOC evaluative research project are to:Test the efficacy of the GEDI MOC by comparing the outcomes of all people aged 70 years or older who presented to a South East Queensland ED before the implementation of the GEDI MOC with those in the 12 months following implementation. Outcomes measured will be: rates of ED representation within 72 h and 28 days, mortality, ED and hospital LoS, time to referral, time to disposition and hospital admission rates;Describe and explore the structures and processes required for the effective delivery of the GEDI MOC;Conduct an economic evaluation of the GEDI MOC.

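### Study 3 calls GEDI cost effective on a test that compares money with money, which can support only a claim of cost saving

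*Protocol article*

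**What the plan says.** The Data analysis section of Study 3 sets out a chain of four steps.

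- A cost function gives average cost per patient before and after GEDI. It allows for "important determinants of individual cost such as age, severity, length of stay and procedures received while in the ED".
- The effect measure is admissions: "we will estimate the average difference in number of admissions for the before- and after-GEDI scenarios".
- That effect is then priced: "The number of avoidable admissions will be converted to cost savings using the results of the cost analysis above". The resulting sum is "compared against the implementation cost for the GEDI MOC".
- The conclusion follows: "If the cost savings is larger than the implementation cost, the GEDI MOC can be viewed as cost effective".

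Elsewhere the article takes a wider view of benefit. The Abstract gives the purpose of GEDI as to "maximise the quality of care for this vulnerable cohort in a cost effective manner". The Study aims list "rates of ED representation within 72 h and 28 days, mortality, ED and hospital LoS, time to referral, time to disposition and hospital admission rates" as outcomes. The Discussion says that "the GEDI MOC aims to facilitate community care strategies and thus acts as a hospital substitution model".

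**The concern.** Cost saving and cost effective are different conclusions. The first needs only costs. The second needs costs and a health effect, or at least evidence that health is no worse. The rule in Study 3 has one effect measure, admissions, and converts it to money before the comparison is made, so nothing about patients' health remains.

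This matters more here than in most service evaluations. In a model meant to substitute for hospital care, a fall in admissions is the change whose safety has to be shown. The rule counts every admission avoided as gain. The outcomes that would show whether patients were safely kept out of hospital are analysed in Study 1, but nothing carries them into the Study 3 verdict. A report could therefore state that GEDI is cost effective while its own Study 1 tables show more deaths or more returns.

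**Working it through.** The article gives no cost, threshold or expected saving, so there is no stated figure to reproduce. The check is to write the rule out and see what it responds to.

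**The rule.** Let A be admissions avoided, c the cost per admission taken from the cost analysis, and I the implementation cost. The stated condition is A × c > I.

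**What it responds to**
- *Deaths.* There is no term for them. If deaths affected c at all, it would be through resources used, not as a loss of health. The disposition outcome in Study 1 lists death separately from admission, so a death in the ED could even count as a presentation without admission.
- *Returns discharged from the ED.* No term.
- *Returns that end in admission.* If admissions are counted per presentation, these reduce A, so they are at least partly inside the rule.

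**Scale**

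From the article:
- Presentations (Setting): 52,410 × 0.18 = 9,433.8, about 9,434 a year.
- GEDI nursing staff (Intervention): 2.4 + 0.8 = 3.2 FTE.

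Assumed, because the article gives no costs: 100,000 to 150,000 per FTE and 3,000 to 8,000 per admission. Physician time is left out.
- Implementation cost: 3.2 × 100,000 = 320,000 to 3.2 × 150,000 = 480,000.
- Fewest admissions needed: 320,000 / 8,000 = 40, which is 40 / 9,433.8 = 0.42 percentage points.
- Most admissions needed: 480,000 / 3,000 = 160, which is 160 / 9,433.8 = 1.70 percentage points.

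**One worked case** (assumed I = 400,000 and c = 5,000)
- A net 2-point fall in admissions is 0.02 × 9,433.8 = 188.7.
- The saving is 188.676 × 5,000 = 943,380, and the net saving is 943,380 − 400,000 = 543,380. The rule is met.
- Let mortality rise by 1 point, or discharged returns rise by 3 points, or both. The net saving stays at 543,380 and the verdict does not change.

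**The part that is captured.** Suppose instead that the 2-point fall is counted before any extra returns. A 3-point rise is 0.03 × 9,433.8 = 283.0 returns. Suppose also that 60% are admitted, the general figure in the article's Background. That adds 283.014 × 0.6 = 169.8 admissions. The net figure becomes (188.676 − 169.808) × 5,000 − 400,000 = about −305,660, and the rule is no longer met. The point must therefore be confined to deaths and to returns discharged from the ED.

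**The case against.** Four things can be said for the plan.

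*Harm would be visible.* The studies belong to one evaluation, and Study 1 reports effects with 95% confidence intervals. This stands, but the economic verdict would still sit beside those results unqualified.

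*The economic question is about costs only.* The research questions in the Study design section do ask only about costs, and the comparison answers that. But an answer about costs is a statement of cost saving, so this supports the change of label.

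*An article condenses a fuller plan.* It does, and a missing ratio or threshold would be no finding. Here, though, the article states a rule and the conclusion to be drawn from it.

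*Savings with equal outcomes would justify the term.* Correct, but equal outcomes is the condition that the rule omits.

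Three stronger readings are tempting and are not supported.
- A reader might infer that a GEDI which improved outcomes at a net cost could never be called cost effective. The sentence says if, not only if. With the same assumed costs, a 0.5-point fall in admissions gives 0.005 × 9,433.8 × 5,000 − 400,000 = about −164,155. The rule is then silent; it does not declare failure.
- A reader might turn a percentage point of mortality into a number of people. The volume in the Setting section counts presentations, and frail older people return.
- A reader might want the verdict to depend on an interval for 30-day mortality excluding a set worsening. The listed mortality outcome covers in-hospital deaths only. A substitution model can lower it by moving deaths elsewhere, so such a test could pass in the situation it is meant to catch. The documents also offer no margin.

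**Conclusion.** The point holds in this form: meeting the Study 3 rule shows that GEDI is cost saving, and cost effective does not follow. At given admissions and costs, the verdict is unaffected by deaths and by returns discharged from the ED, whatever their size. That follows from the form of the rule and needs no assumed figure. The break-even range of 40 to 160 admissions a year does rest on assumed unit costs. It shows only that a modest fall could trigger the verdict; it does not measure likely harm.

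The cost estimates themselves are not affected. What changes is the conclusion that may be drawn from them. The article states no other route to a cost-effectiveness conclusion, though it does not rule one out.

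**What to change.** 1. In the Study 3 decision rule, replace cost effective with cost saving.
2. Report net cost with its uncertainty in a cost-consequence table, beside the Study 1 changes in mortality and in 72 h and 28-day re-presentation.
3. State that no claim of cost effectiveness will be made from net saving alone, or where those outcomes are worse.
4. Note that the mortality outcome listed under Data collection for Study 1 covers in-hospital deaths only, and show out-of-hospital deaths in the same table. The Study 1 analysis already relies on them as a competing risk for re-presentation.
5. Say whether admissions are counted per presentation, so that a reader can tell how far returns ending in admission are already in the saving.

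The cost is a few sentences and one table. No outcome is needed beyond those that the Study 1 analysis already uses. The downside is a narrower headline economic claim.
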